#### Postacute COVID-19 (long-COVID-19)

To assess for the presence, or absence, of postacute COVID-19 symptoms, patients will be presented with the same 13-item measure (fever, cough, shortness of breath or difficulty with breathing, headaches, aches and pains, fatigue/tiredness, nausea, diarrhoea, sore throat, loss of appetite, loss of taste, loss of smell and an additional open-ended option for ‘other’) as the COVID-19 symptomatology questionnaire. However, they will be asked to indicate whether they continued experiencing the symptom for more than 2 weeks following their diagnosis and/or are still currently experiencing the symptom.

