Second, patient symptom profiles of COVID-19 and postacute COVID-19 will be identified using a quantitative method approach (objective 2). Identifying patient symptom profiles of COVID-19 and postacute COVID-19 may highlight potential subgroups of patients who may be more likely to present with higher symptomatology or different sets of co-occurring symptoms. In addition, predictors, such as demographic variables and pre-existing comorbidities, of the COVID-19 symptom profiles will be determined. Identifying these predictors may be of particular benefit to identifying patients who may need to be monitored for a longer duration. For example, identifying patients who are likely to remain symptomatic (particularly symptoms such as shortness of breath) may need to be monitored for a longer duration after acute COVID-19. Furthermore, identifying such profiles may aid COVID-19-positive patients in being prepared for a likely set of symptoms that they may experience long term, depending on the predictors of the COVID-19 symptom profiles. For example, identifying patients who are likely to have persistent symptoms such as fatigue and loss of taste/smell may be useful in helping the patient being prepared for these long-term effects.

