#### COVID-19 symptomatology

Patient experience of COVID-19 will be measured via a 13-item measure that assesses the presence, or absence, of COVID-19 symptoms. This measure consists of 12 commonly reported COVID-19 symptoms (fever, cough, shortness of breath or difficulty with breathing, headaches, aches and pains, fatigue/tiredness, nausea, diarrhoea, sore throat, loss of appetite, loss of taste and loss of smell) and an additional open-ended option for ‘other’. For each symptom, participants will be asked to indicate whether they experienced the symptom in the first 2 weeks following their diagnosis.

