#### Pre-existing comorbidities

Pre-existing comorbidities (ie, prior to a diagnosis of COVID-19) will be assessed via a nine-item list of physical comorbidities such as chronic respiratory disease and chronic heart disease. Responses will be scored using a trichotomous response format (‘yes’, ‘no’, ‘unknown’).

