Third, latent classes, or symptom profiles, of COVID-19 and postacute COVID-19 will be examined through latent class analysis (LCA), using robust maximum likelihood estimation. To determine the optimal number of latent classes, models with one to six classes will be examined. To avoid solutions based on local maxima, 500 random sets of starting values will be used followed by 100 final stage optimisations. Several fit indices will be used to determine the fit of each latent class model, including the Akaike information criterion (AIC),^50^ the Bayesian information criterion (BIC),^51^ the sample size-adjusted BIC (ssaBIC),^52^ entropy values and the Lo-Mendell-Rubin-adjusted likelihood ratio test (LMR-A).^53^ Lower AIC, BIC and ssaBIC values and higher entropy values are indicative of better model fit. A non-significant LMR-A value suggests that the model with one less class should be accepted. In the event that an insufficient sample size is gathered, then a cluster analysis will be conducted instead.

Next, to determine the predictors of each symptom profile, a multinomial logistic regression will be performed by regressing the latent classes (identified during the class enumeration process) onto several covariates, using the R3STEP function in Mplus.^54 55^ This three-step procedure involves first identifying the most appropriate latent classes; then obtaining the most likely class memberships based on the posterior probabilities of the LCA, while accounting for the classification uncertainty rate (ie, measurement error) and, finally, the most likely class memberships are analysed with the covariates, thereby accounting for at least some of the misclassification errors.^55 56^

Fourth, the interviews will be transcribed verbatim. A thematic analysis will be conducted using NVivo V.12^57^ to identify common themes throughout the interviews. An inductive approach will be taken to draw out themes, without a pre-existing theory in the literature or based on the researchers’ preconceptions, by one researcher through familiarisation with the data, initial coding, refinement and subsequently grouped into themes to best represent the data. It will then be reviewed by the research team to ensure that all emerging topics are included and consensus is reached. A secondary researcher will independently code a subset of transcripts to assess the internal reliability.

### Measures: work package 2

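### Neither symptom list, as described, asks whether a symptom is new or worse than before COVID-19, so associations between comorbidities and symptom profiles can be spurious or inflated

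*Protocol article*

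**What the plan says.** The symptom outcome rests on two uses of one list. Under COVID-19 symptomatology, the protocol article describes a "13-item measure that assesses the presence, or absence, of COVID-19 symptoms", in which "participants will be asked to indicate whether they experienced the symptom in the first 2 weeks following their diagnosis". Under Postacute COVID-19 (long-COVID-19), "patients will be presented with the same 13-item measure" and are asked "whether they continued experiencing the symptom for more than 2 weeks following their diagnosis and/or are still currently experiencing the symptom". The list includes cough, breathlessness, headaches, aches and fatigue as well as loss of taste and loss of smell.

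Under Pre-existing comorbidities, the article describes a "nine-item list of physical comorbidities such as chronic respiratory disease and chronic heart disease", answered yes, no or unknown. This records diagnoses. No measure described for work package 1 records which symptoms the patient had before infection.

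The Introduction states under objective 2 that "predictors, such as demographic variables and pre-existing comorbidities, of the COVID-19 symptom profiles will be determined". Data analysis: work package 1 carries this out by "regressing the latent classes (identified during the class enumeration process) onto several covariates, using the R3STEP function in Mplus".

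**The concern.** Breathlessness, cough and fatigue are non-specific. A patient who has had them for years because of chronic respiratory or heart disease can truthfully tick them as present in the first 2 weeks, as lasting beyond 2 weeks and as present now. The latent classes are built from those ticks and then regressed on the comorbidities that may have produced them. The outcome can thus partly reflect the predictor.

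The Introduction gives two uses for the results: picking out patients who may need longer monitoring, with breathlessness as the example, and telling patients which long-term symptoms to expect. An association that reflects the state before COVID-19 would mislead on both. The limitations listed with the abstract cover generalisability and temporal ordering; they do not mention symptoms present before infection.

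**Working it through.** The article gives no sample size, power or prevalence for this analysis, so there is no stated figure to reproduce. The check has two parts.

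**Can the planned analysis remove the overlap?** The three-step procedure allows for uncertainty in assigning patients to classes. It does not address symptoms that COVID-19 did not cause. Entering the comorbidity as a covariate only estimates the contaminated association. Separating the two needs information on symptoms before infection, and none is described.

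**How large could the effect be for one symptom item?** All rates here are assumptions.

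- t = probability that COVID-19 causes the symptom, set equal with and without the comorbidity, so the true odds ratio (OR) is 1.
- b1, b0 = probability that the symptom was already present before COVID-19, with and without the comorbidity.
- Every symptom present is ticked, so P(ticked) = 1 − (1 − t)(1 − b).
- OR = [p1/(1 − p1)] / [p0/(1 − p0)].

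Worked case, t = 20%, b1 = 50%, b0 = 5%: p1 = 1 − 0.80 × 0.50 = 0.60; p0 = 1 − 0.80 × 0.95 = 0.24; OR = (0.60/0.40)/(0.24/0.76) = 4.75.

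| t | b1 v b0 | Ticked, with v without comorbidity | OR (true 1) |
|---|---|---|---|
| 10% | 10% v 2% | 19.0% v 11.8% | 1.75 |
| 10% | 50% v 5% | 55.0% v 14.5% | 7.21 |
| 20% | 20% v 5% | 36% v 24% | 1.78 |
| 20% | 30% v 5% | 44% v 24% | 2.49 |
| 20% | 50% v 5% | 60% v 24% | 4.75 |
| 30% | 10% v 2% | 37.0% v 31.4% | 1.28 |
| 50% | 50% v 5% | 75.0% v 52.5% | 2.71 |
| 70% | 10% v 2% | 73.0% v 70.6% | 1.13 |
| any | 5% v 5% | equal | 1.00 |

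For t of 10% to 30% the spurious OR runs from 1.28 to 7.21. For common symptoms (t of 50% to 70%) it runs from 1.13 to 2.71. It vanishes when baseline prevalence is equal.

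**Could it reach significance?** The article gives 925 discharged patients but no response rate. Assume 15% have the comorbidity and 20%, 40% or 100% respond (N = 185, 370 or 925). In the 44% v 24% case, the chance of a two-sided p < 0.05 is about 58%, 85% and over 99%. In the 73.0% v 70.6% case it is about 4%, 5% and 8%.

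**What would an anchor do?** If only new or worse symptoms count, b drops out. Both groups tick at rate t and the OR returns to 1.0.

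**What if pre-existing symptoms were simply scored absent?** Then P = t(1 − b), because worsened symptoms are dropped too. With t = 20% and b0 = 5%:

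- b1 = 50%: 0.20 × 0.50 = 10% v 0.20 × 0.95 = 19%, OR = (0.10/0.90)/(0.19/0.81) = 0.47.
- b1 = 20%: 0.20 × 0.80 = 16% v 19%, OR = (0.16/0.84)/(0.19/0.81) = 0.81.

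The bias reverses and the comorbidity looks protective.

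**The case against.** **The questionnaire is not shown.** Its instructions might contain an anchor, and the labels 'COVID-19' and 'post-acute COVID-19', or the word 'continued', may lead some patients to leave out old symptoms. This stands as a caution. But the article does describe the question put to patients, and that description has no anchor. 'Continued' points back to the acute item, which has the same gap, and the limb about current symptoms is open to any chronic complaint. Self-exclusion would shrink the bias by an unknown amount.

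**The aim is largely predictive.** A patient who stays breathless may need monitoring whatever the cause. That is fair for pure prediction. But the article presents the profiles as those of COVID-19 and post-acute COVID-19 and wants to tell patients what to expect from the illness, which requires attribution.

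**The illustration is not the planned estimand.** This stands. A single-item OR does not translate directly into a class-membership OR from a multinomial model, and no document figure fixes the inputs.

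**Stronger readings are not supported.** A reader might infer that comorbidities will be found to predict the profiles, or that the profiles are merely comorbidity clusters. The text shows a risk, not a result. Only two of the nine conditions are named, and items such as loss of taste or smell should be little affected. A reader might also infer that nothing can be done at analysis. In fact the comorbidity list allows the classes to be re-estimated in patients without the named chronic diseases. That tests whether the profiles persist, although it cannot recover an uncontaminated comorbidity coefficient.

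**Conclusion.** The point holds as a risk of bias in the predictor part of objective 2. As described, the symptom items have no pre-COVID reference, prior symptoms are not recorded, and comorbidities that can cause the same symptoms are used as predictors. Where those diseases raise baseline symptom prevalence, the bias is upward, and the three-step method does not remove it.

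The size cannot be fixed from the document. The OR range of about 1.1 to 7 rests on assumed rates, an equal COVID-19 effect in both groups and full reporting of pre-existing symptoms, and it applies to single items only. The exposure is greatest for non-specific symptoms that COVID-19 itself causes less often. The change is worth making because it is cheap and bears on a stated objective.

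**What to change.** Add 'new, or worse than before you had COVID-19' to every item in both symptom lists, and build the latent class indicators from new-or-worse responses. The cost is a few words in an online survey, whatever approval that change needs (the article does not say how amendments are classified), and one more recall judgement for each respondent.

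If the survey can no longer be changed for some respondents, repeat the latent class analysis among patients without chronic respiratory or heart disease as a sensitivity analysis, accepting the smaller sample. Report the comorbidity associations as not separable from baseline symptoms. Do not score pre-existing symptoms as absent: that discards genuine worsening and biases the association the other way.

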#### Pre-existing comorbidities

Pre-existing comorbidities (ie, prior to a diagnosis of COVID-19) will be assessed via a nine-item list of physical comorbidities such as chronic respiratory disease and chronic heart disease. Responses will be scored using a trichotomous response format (‘yes’, ‘no’, ‘unknown’).

#### Prior experience with mobile phone applications

To measure prior experience with smartphone applications, participants will be presented with five statements to which they chose the most appropriate statement (ranging from ‘I have never used a mobile phone app prior to the COVID-19 app’ to ‘I use mobile phone apps regularly to upload and track my activity’).

#### User acceptance of remote monitoring equipment

Patients who report using either a pulse oximeter and a remote monitoring phone application, or just the remote monitoring phone application will be asked to complete a 16-item questionnaire pertaining to their experience of the technology. This multidimensional measure is comprised of items relating to the different factors of user technology acceptance, based on a recent integrated model consisting of factors from the UTAUT and TTF models^33^. Several factors will be extracted from this model, consisting of ‘social influence’ (two items; the degree to which important others agree to the use of the technology; for example, ‘people who influence my behaviour thought it was important that I use the remote monitoring equipment’), ‘facilitating conditions’ (three items; individual’s perception of the availability of resources to use the technology; for example, ‘I felt I had the necessary knowledge to use the remote monitoring equipment’), ‘effort expectancy’ (four items; ease-of-use related to using the technology; for example, ‘I find it easy to use such equipment’), ‘performance expectancy’ (four items; effectiveness to users in performing specific tasks; for example, ‘I feel remote monitoring equipment is useful in obtaining health information’) and ‘TTF’ (three items; the degree to which users believe that the performance of the technology matches its intended use; for example, ‘In general, the remote monitoring equipment fully met my needs’). All items will be rated using a five-point Likert scale (‘strongly disagree’=1, ‘strongly agree’=5), with higher scores reflecting greater scores towards its respective factor. Previous psychometric research has supported the validity and reliability of these items.^33^ Participants will also have the opportunity to share any additional information about their experience through an open-ended question.

#### Adherence to the use of remote monitoring equipment

Adherence to the use of the pulse oximeter throughout the intervention will be assessed via three statements with participants being asked to choose the statement that best reflects their experience (‘I did not use the oximeter’, ‘I tried to use the oximeter but gave up because it was too difficult’, ‘I occasionally used the oximeter during my treatment’ and ‘I used the oximeter consistently during my treatment’). In addition, participants will have the option to share any additional information about their experience of using the device through an open-ended question. Adherence to the use of the remote monitoring phone application will be assessed via three statements with participants being asked to choose the statement that best reflects their experience (‘I did not use the phone application to record my symptoms’, ‘I tried to use the phone application but gave up because it was too difficult’, ‘I occasionally used the phone application to record my symptoms throughout my treatment’ and ‘I used the phone application to record my symptoms consistently throughout my treatment’). In addition, participants will have the option to share any additional information about their experience of using the phone application through an open-ended question.

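### The oximeter adherence options cannot separate patients never given the device from patients who did not use it, and the gave-up option for both devices allows only one reason; the announced count of three statements should also read four

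*Protocol article*

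**What the plan says.** The section Adherence to the use of remote monitoring equipment introduces the two items in parallel. For the oximeter, and again for the phone application, it says that adherence "will be assessed via three statements with participants being asked to choose the statement that best reflects their experience". Four oximeter statements are then printed. The first is "I did not use the oximeter". The second, which carries a reason, is "I tried to use the oximeter but gave up because it was too difficult". The other two describe occasional and consistent use. The application item has four matching statements, and each item is followed by an optional free-text question.

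The section User acceptance of remote monitoring equipment directs its questionnaire to patients who report using both devices, "or just the remote monitoring phone application will be asked to complete a 16-item questionnaire". The article thus expects some respondents to report using the application alone.

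Data analysis: work package 1 places adherence in the opening descriptive step for the first objective, alongside patient–professional interaction and acceptance. It gives no scoring rule or denominator for adherence, and does not name adherence among its example covariates for the structural equation model.

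**The concern.** There are three separate matters.

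1. The announced number of statements disagrees with the number listed, for both devices.
2. A patient who never had an oximeter and is shown the oximeter item can truthfully choose only "I did not use the oximeter". A patient who had one and ignored it gives the same answer. One is a fact about supply, the other about behaviour.
3. The statement "I tried to use the oximeter but gave up because it was too difficult" joins two facts, that the patient stopped and why. The application item is built the same way. Someone who stopped for any other reason must either endorse a cause that did not apply or choose the occasional-use statement.

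At stake is whether the reported oximeter adherence describes what patients did with the device. The response options are printed in full, so their content is fixed in this article and not deferred to another document.

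**Working it through.** **Count of statements.** Oximeter: announced 3, listed 4 (not used; tried and gave up; occasional; consistent). Application: announced 3, listed 4, in the same pattern. Both differ by one. Nothing sets the not-used statement apart from the other three, so the natural reading is a four-category item with a miscount in the lead-in.

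**Whether issue status is recorded.** The patient survey measures described run from Demographic information to Perceived patient-centred care. They cover demographics, acute and postacute symptoms, comorbidities, prior application experience, acceptance, adherence and patient–professional interaction. None asks what equipment the patient was given. The acceptance section relies on reported use, which is not the same as issue: a patient given an oximeter who never used it would also report using only the application.

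**What follows for the denominator.** Let f be the share of respondents never issued an oximeter, and let c and x be the shares of consistent users and non-users among those issued one.

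- If everyone answers and all are counted, reported consistent use is c(1 − f). Reported non-use is f + (1 − f)x, which exceeds x by f(1 − x).
- If the item is routed on reported use, true non-users leave the denominator too, and reported consistent use becomes c/(1 − x).
- The quantity wanted is c. The described survey items identify it only if f = 0 in the first case or x = 0 in the second.

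**Illustration only.** The article gives none of f, c or x. Assume c = 0.85 and f between 0.10 and 0.40; x then lies between 0 and 0.15.

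- All counted, consistent use: 0.85 × 0.90 = 0.765 at f = 0.10, and 0.85 × 0.60 = 0.51 at f = 0.40.
- All counted, excess in reported non-use: at f = 0.10, from 0.10 × 0.85 = 0.085 to 0.10 × 1 = 0.10; at f = 0.40, from 0.40 × 0.85 = 0.34 to 0.40 × 1 = 0.40. The 10 and 40 point figures are thus the upper limits, reached at x = 0.
- Routed on reported use, consistent use: from 0.85/1 = 0.85 at x = 0 to 0.85/0.85 = 1.00 at x = 0.15.

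The two approaches err in opposite directions. The sizes depend entirely on the assumed inputs.

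**Gave-up option.** No arithmetic applies. Of the four statements, only one describes stopping, and it carries a single cause. The free-text question may collect other reasons, but it is optional and does not change the coded answer.

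**The case against.** A reader might infer that patients without an oximeter are counted as non-adherent. The article does not support that. It would require that some patients were not issued an oximeter, that they are shown the item, and that non-use is scored as non-adherence over all respondents. None of these is stated. A patient reporting application use alone may have had an oximeter, and a four-category table would show non-use as its own row. That objection stands.

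It is also fair that a journal article commonly leaves skip logic and item coding to the questionnaire or the full protocol, and that their absence is no fault. This stands too, but it does not dispose of the point. Routing on the one equipment variable described, reported use, would remove true non-users along with unsupplied patients. The missing category lies in the printed options themselves.

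On the gave-up option, one can reply that patients choose the best fit, can explain in free text, and that no analysis of reasons for stopping is announced. A claim that difficulty will be overstated as a cause therefore goes beyond the plan. What remains is narrower: these patients have no accurate coded answer.

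Finally, adherence is not the modelled outcome. The first objective is acceptance, examined by modelling and interviews, so the importance should not be inflated. The miscount, with every option printed, has no analytic consequence.

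**Conclusion.** The point holds in a limited form. The three-against-four mismatch is certain, occurs twice, and is clerical. The oximeter options do not separate non-supply from non-use, and no described survey item recovers the difference, so the adherence summary may mix supply with behaviour. Whether it does depends on whether any respondents were not issued an oximeter, which the article does not say. The gave-up wording leaves patients who stopped for other reasons without a correct category, for both devices.

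The consequence is confined to a descriptive summary; no hypothesis test or sample size is affected. The size cannot be computed from the article, and the percentages above are illustrations under stated assumptions. The change is still worth making because it is cheap and because the described survey items could not supply the distinction afterwards.

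**What to change.** 1. Change the announced number of statements to four for both devices.
2. Add a response such as 'I was not given this device' to each item, or take issue status from clinic records.
3. State that adherence is summarised among patients issued the device, and show the number not issued it separately.
4. Reword the gave-up statement to 'I started but stopped using it' for each device, and ask the reason in a separate short question.

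The cost is one added option, one reworded option and one brief reason question per device, with no extra participants. The wording changes need to be in place before the survey goes out. If it has already gone out, clinic records are the remaining source for issue status. Because the research team receives deidentified data, the hospital would then have to attach that status before transfer.

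Entering equipment type as a covariate in the acceptance model is a separate, optional suggestion; this point does not depend on it.
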